**Fig. 1 Fig1:**
[figure not shown]
Implementation and effectiveness evaluation populations selection flow. BP = blood pressure

### Implementation strategies

The implementation strategies used in this study aim to promote fidelity to the hypertension detection and treatment protocol recommended by the South African Hypertension Society Guidelines [26]. The implementation strategies were designed through community-engaged formative work that was guided by the Behavior Change Wheel [27]. Details and results from our formative work are reported elsewhere [21]. Briefly, we conducted interviews with relevant actors (patients, clinicians, and administrators) to identify barriers to detecting and treating elevated blood pressure (for healthcare workers), or to managing it (for patients). The barriers identified were reviewed and ranked by the study’s Community Advisory Board and a final set of barriers to be addressed in the study was selected. These barriers were then mapped onto relevant intervention functions and behavior change techniques specified in the Behavior Change Wheel [27].

Four implementation strategies resulted from our formative work: identify and prepare care champions, change record systems, conduct ongoing training, and audit and provide feedback. Because blood pressure assessment equipment was lacking in participating clinics, a fifth implementation strategy was added –changing the physical structure and equipment. The five implementation strategies tested in this study are described in Table 2. These were defined using Expert Recommendations for Implementing Change [28] and specified according to established recommendations [29]. The implementation strategies will be carried out by the study care coordinator during the active intervention period. During the maintenance period, the care coordinator will be withdrawn, and the implementation strategies will be carried out by clinic staff.

**Table 2 Tab2:** Implementation strategy specification

Name	Specification^a^ (actor, action, target)	Temporality and dose
Identify and prepare care champions	Care coordinator recruited and trained to assist healthcare workers with implementation of the elevated blood pressure detection and treatment protocol.	Throughout active intervention period
Change record systems	Information management system that includes a dashboard summarizing blood pressure data each month (e.g., case detection and treatment rates), and patient flow charts to record data on blood pressure assessment results and treatment. The dashboard is updated by research staff and presented by the care coordinator at a monthly clinic meetings.	Throughout active intervention period
Conduct ongoing training	Ongoing training sessions for healthcare workers delivered by the care coordinator on elevated blood pressure detection and treatment, data interpretation, and patient-provider communication skills.	Monthly: during active intervention period
Change physical structure and equipment	Dinamap™ and portable blood pressure assessment machines placed at participating clinics used and maintained by the care coordinator.	At intervention rollout
Audit and provide feedback	Sessions delivered by the care coordinator where the dashboard data for a given month is presented to healthcare workers, clinic managers, and staff. Programmatic feedback is provided to discuss how to improve case detection and treatment.	Monthly: during active intervention period

^a^During the maintenance period, the care coordinator (actor) will be withdrawn, and all the activities specified in each implementation strategy will be carried out by clinic staff

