### Study populations

 The study includes two analytic study populations: the implementation evaluation and the effectiveness evaluation population. Figure 1 shows the implementation and effectiveness population selection flow. The implementation evaluation population will include all patients ≥ 18 years old who present to clinic for care and are seen in the study triage room where vital signs are taken. Data from this population will be collected by a research staff member situated in the triage room who will record whether blood pressure is measured, the blood pressure values obtained, and whether educational materials are delivered at each visit. These data will be recorded using a REDCAP form developed for the study. These patients will contribute data to the primary implementation outcome for all study steps, including control and intervention periods.

The effectiveness evaluation population will include patients aged ≥18 years old with elevated blood pressure (defined as systolic blood pressure ≥140 mmHg or diastolic blood pressure ≥90 mmHg), at any point during the active intervention period, and with a known diagnosis of HIV (determined by self-report or medical chart review). Patients are eligible regardless of their prior history of hypertension or use of blood pressure lowering medications. Research staff situated in the triage vitals room will recruit these patients and obtain consent to prospectively abstract demographic and clinical data from their medical charts. Patients will be included in the study through continuous recruitment. Patients with HIV and elevated blood pressure then become part of the effectiveness outcome population from the date of their first elevated blood pressure value is recorded and will remain under observation for all additional study visits.

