**IMPLEMENTATION EVALUATION**		
**Outcome definitions **	**Time points**	**Data source**
***Adoption*** Participation rate and representativeness of clinics that initiate the blood pressure assessment intervention	At every initial study step (i.e., just the initial rollout step)	• Study REDCAP form
***Implementation Fidelity*** Primary implementation outcome: extent to which the BP measurement protocol is implemented	All clinic visits in months 1–15, excluding the two months following intervention initiation (during research staff implementation phase)	• Medical charts • Study REDCAP form • Adaptations recorded by care coordinator / research staff
***Cost*** Initial costs of implementation strategies and cost of implementing the BP measurement protocol	Control, intervention (months 1–15) and maintenance (months 16–27) periods	• Study records • Time and motion assessment
***Clinic-level Maintenance*** Extent to which BP continues to be measured and is normalized after active intervention period	Months 16–27 (during clinic staff implementation)	• Medical charts • Healthcare worker normalization questionnaire

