**EFFECTIVENESS EVALUATION**		
**Outcome definitions**	**Time points**	**Data source**
***Reach*** Percentage and representativeness of patients with elevated blood pressure and HIV that receive the intervention	At the initial / enrollment study visit (months 1–15)	• Study REDCAP form • Medical charts
***Effectiveness*** Primary clinical outcome: difference in mean systolic BP between the intervention and control periods	All visits in months 1–15, excluding the two months following intervention initiation	• Medical charts
***Cost-effectiveness*** Health utility of the intervention and direct medical costs of additional patient visits and/or hospitalizations	Control, active intervention (months 1–15), and maintenance periods (months 16–27)	• Quality of life (EQ-5D) patient questionnaire • Patient-reported cost survey • Study records
***Patient-level Maintenance*** Extent to which blood pressure improvements observed during the intervention phase are maintained	Active intervention (months 4–15) and maintenance (months 16–27) periods	• Medical charts • Study REDCAP form

*BP* blood pressure

*Adoption* will be determined as the percentage and representativeness of clinics that complete the blood pressure assessment protocol at the initial study step (i.e., did they roll out intervention? Yes/No). Intervention fidelity (*primary implementation outcome*) will be defined as the difference in percentage of patient visits with recorded blood pressure measurement between intervention and control periods. We will also keep track of adaptations made to the blood pressure assessment protocol via care coordinator notes and reports. Clinic-level *maintenance* of the intervention will be defined as the extent to which blood pressure continues to be assessed after the active intervention period ends based on medical chart reviews. We will also assess the normalization of the blood pressure assessment protocol using a 23-item questionnaire [32] healthcare workers will complete at the beginning and at the end of the maintenance period.

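### The primary systolic outcome is sourced from medical charts alone, while the tested package changes blood pressure recording at crossover; the triage REDCap readings should be added as a source or check

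*Protocol article*

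**What the plan says.** **The intervention.** Table 2 (Implementation strategies) includes a change of record systems among the five strategies. Besides a monthly dashboard it supplies "patient flow charts to record data on blood pressure assessment results and treatment", in use for the whole active intervention period.

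**The systolic outcome.** The Effectiveness row of Table 3 reads "Primary clinical outcome: difference in mean systolic BP between the intervention and control periods" and gives one data source: "Medical charts". The Study populations section agrees: research staff obtain consent to "prospectively abstract demographic and clinical data from their medical charts". The Patient-level Maintenance row of the same table lists charts and the REDCap form together, and its time points include months 4–15.

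**Fidelity.** Table 3 describes it as "Primary implementation outcome: extent to which the BP measurement protocol is implemented" and lists "Medical charts • Study REDCAP form • Adaptations recorded by care coordinator / research staff". Outcome measures and definitions words it as the "difference in percentage of patient visits with recorded blood pressure measurement between intervention and control periods". The Implementation outcomes analyses section codes the variable as measured or not measured.

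**The independent source.** Study populations describes a member of the research staff, posted at triage, "who will record whether blood pressure is measured, the blood pressure values obtained, and whether educational materials are delivered at each visit". This goes onto a REDCap form, and these patients feed the primary implementation outcome in both control and intervention periods.

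**The concern.** A treatment comparison needs the outcome to be ascertained in the same way under both conditions. Here a tool for writing down blood pressure is part of the treatment, and the primary systolic outcome is read from written records. If the flow chart makes charting more complete after crossover, the set of readings that reaches the analysis changes at the same moment as exposure.

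The analysis as described would not remove such a change. Period effects absorb what is common to all clinics in a calendar period, but this change follows each clinic's own crossover. Leaving out the first two months after initiation does not help either, because the flow charts stay in use. The mixed model uses only readings that reach the chart.

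What is at stake is the interpretation of the effectiveness result: part of an apparent fall in systolic pressure could be a fall in selective record-keeping. A source that the record-system strategy does not alter is already being collected.

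**Working it through.** **Inputs from the protocol.** SD of systolic pressure 20 mmHg and target difference 5 mmHg (Sample size calculation); cut-point 140 mmHg, the systolic threshold for elevated pressure (Study populations).

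**Inputs assumed.** The protocol gives no charting rates and no mean. I take true mean 142 mmHg in both conditions (no real effect) and a normal distribution. Control charting is 95% for readings of 140 or more and *r* for lower ones. After crossover, charting is unrelated to level.

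**Formula.** With a = (140 − 142)/20 = −0.1:

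- share at or above 140: p = 1 − Φ(−0.1) = 0.540; share below: 0.460
- mean of the high readings: 142 + 20 × 0.397/0.540 = 156.7
- mean of the low readings: 142 − 20 × 0.397/0.460 = 124.7
- charted control mean = (p × 0.95 × 156.7 + (1 − p) × r × 124.7) / (p × 0.95 + (1 − p) × r)

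| Charting of readings below 140 (*r*) | Charted control mean | Excess over 142 |
|---|---|---|
| 95% (loss unrelated to level) | 142.0 | 0 |
| 85% | 142.9 | 0.9 |
| 75% | 143.9 | 1.9 |
| 60% | 145.5 | 3.5 |

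The assumed mean matters little: from 135 to 145 mmHg the last three rows give about 0.9, 1.8 to 1.9 and 3.3 to 3.7.

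**What drives the result.** It is the contrast in charting between high and low readings, not the total loss. Charting 90% of all control readings and 95% of all intervention readings gives a difference of 0. A steeper assumption, 90% against 50%, gives 4.2 to 4.7 mmHg over the same range of means. If some selectivity persists after crossover (95% against 90%), the 3.5 mmHg becomes 3.1.

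**Fidelity, only if scored from charts alone.** Spurious rise = share measured × change in charting completeness. With 70% of visits measured in both conditions (assumed):

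- charting 90% to 98%: 0.70 × 0.08 = 5.6 points
- charting 80% to 98%: 0.70 × 0.18 = 12.6 points
- charting 70% to 95%: 0.70 × 0.25 = 17.5 points

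Scored from the triage REDCap form, the charting artefact is about zero.

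**The case against.** A reader might infer that better charting can appear as an effect on both co-primary outcomes. The protocol does not support that for fidelity. Research staff observe in triage whether pressure is measured, these patients feed the primary implementation outcome in both conditions, and the analysis variable is measured versus not measured. Charts are listed as a second source without a ranking and the definition speaks of recorded pressure, but an article may leave that ranking to the full protocol. The fidelity figures above apply only to scoring from charts alone, which is not the plan described.

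On systolic pressure the objection is that the mechanism is conjecture. Three conditions must hold: the flow chart is, or feeds, the abstracted chart; control charting depends on the reading; and that dependence fades after crossover. The protocol states none of them, and Table 2 places the flow chart in an information management system that includes a study dashboard. Nor does a normal distribution around 142 mmHg model patients who enter through an elevated reading. All this stands. It makes the size illustrative and the direction conditional. It does not change the fact that the outcome's only listed source is one whose completeness the package may alter.

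The mixed sources in the Patient-level Maintenance row suggest that REDCap readings may be meant for active-period pressure too. That makes the Effectiveness row look incomplete rather than deliberate, and supports amending it.

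Finally, replacing charts outright would not be free. The REDCap form covers triage-room visits, whereas the Effectiveness row specifies all visits, and linkage of triage entries to enrolled patients is not described. This stands and shapes the fix.

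**Conclusion.** The point holds for the systolic outcome as an avoidable ascertainment risk. The only source named in the Effectiveness row of Table 3 may become more complete exactly when a clinic crosses over, and a parallel source observed in both conditions is not listed there. The size is roughly 0 to 3.5 mmHg of spurious benefit against a 5 mmHg target. This rests wholly on assumed charting rates, on a flow chart that feeds the abstracted chart, and on control charting that favours high readings more than intervention charting does. It is zero if charting loss is unrelated to pressure level. The protocol does not show that such bias is present, and the figures should not be read as an estimate of it.

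For fidelity no error is shown. A statement of which source governs would confirm what Study populations and Implementation outcomes analyses already imply.

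**What to change.** 1. In the Effectiveness row of Table 3, add the triage REDCap form as the source for systolic pressure in months 1–15 wherever a triage reading can be linked to an enrolled patient, and keep charts for other visits.
2. If charts must stay the main source, prespecify a sensitivity analysis on the REDCap readings.
3. In either case, report by condition how often a triage reading appears in the chart and how well the two values agree. Reporting the first separately for readings below and at or above 140 mmHg would test the assumption on which the bias depends.
4. For fidelity, add one sentence: where chart and REDCap differ, the REDCap observation governs.

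**Cost.** No new measurement is needed, because the values are already recorded in both conditions. The work is wording, one agreement table, and linkage of triage entries to enrolled patients, after confirming that their consent, described for chart abstraction, covers it. Visits outside the triage room remain chart-only. The observer is unblinded, so the change removes the charting artefact but not every effect of observation. It also cannot recover readings that were never taken.

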### Clinical intervention

The clinical intervention follows the recommendations from the South African Hypertension Society Guidelines [26] and includes the following components: (1) assessing blood pressure, (2) providing patient education, (3) providing brief lifestyle modification advice and, where needed, (4) providing blood pressure lowering medication (Fig. 2). Patient educational materials include color-coded posters placed in clinics and individual pocket-sized booklets explaining blood pressure levels (green = normal, yellow = high/elevated, red = very high), and what to do to lower or maintain blood pressure levels. Booklets also provide a longitudinal record for patients to self-monitor their blood pressure levels over time. All materials are available in English, isiZulu, isiXhosa, and Shona to cater for most of the populations clinics serve. All patients in these clinics receive this intervention regardless of the purpose of the visit or medical history unless they attend during the control period and do not return to the clinic.

**Fig. 2 Fig2:**
[figure not shown]
Intervention theory depicting the hypothesized action mechanisms and outcomes for the implementation strategies and the clinical intervention. BP = blood pressure; LSM = lifestyle modification

### Outcome measures and definitions

Our study outcomes are based on the RE-AIM framework [30]. The two primary outcomes are intervention fidelity to the blood pressure assessment protocol in clinics (*implementation*) and changes in blood pressure in patients with elevated values (*effectiveness).* Secondary outcomes include *adoption*,* cost* and *maintenance* of the blood pressure assessment protocol in clinics, as well as the *reach* and effect *maintenance* of the intervention among patients. Data for these outcomes will be obtained from patient medical charts, direct observation, REDCAP [31] data collection forms designed for this study, patient surveys, study records, and healthcare worker surveys. The RE-AIM outcomes, their assessment time points, and their data sources are reported in Table 3.

**Table 3 Tab3:** RE-AIM outcome definitions, data sources and data collection time points

**IMPLEMENTATION EVALUATION**		
**Outcome definitions **	**Time points**	**Data source**
***Adoption*** Participation rate and representativeness of clinics that initiate the blood pressure assessment intervention	At every initial study step (i.e., just the initial rollout step)	• Study REDCAP form
***Implementation Fidelity*** Primary implementation outcome: extent to which the BP measurement protocol is implemented	All clinic visits in months 1–15, excluding the two months following intervention initiation (during research staff implementation phase)	• Medical charts • Study REDCAP form • Adaptations recorded by care coordinator / research staff
***Cost*** Initial costs of implementation strategies and cost of implementing the BP measurement protocol	Control, intervention (months 1–15) and maintenance (months 16–27) periods	• Study records • Time and motion assessment
***Clinic-level Maintenance*** Extent to which BP continues to be measured and is normalized after active intervention period	Months 16–27 (during clinic staff implementation)	• Medical charts • Healthcare worker normalization questionnaire
**EFFECTIVENESS EVALUATION**		
**Outcome definitions**	**Time points**	**Data source**
***Reach*** Percentage and representativeness of patients with elevated blood pressure and HIV that receive the intervention	At the initial / enrollment study visit (months 1–15)	• Study REDCAP form • Medical charts
***Effectiveness*** Primary clinical outcome: difference in mean systolic BP between the intervention and control periods	All visits in months 1–15, excluding the two months following intervention initiation	• Medical charts
***Cost-effectiveness*** Health utility of the intervention and direct medical costs of additional patient visits and/or hospitalizations	Control, active intervention (months 1–15), and maintenance periods (months 16–27)	• Quality of life (EQ-5D) patient questionnaire • Patient-reported cost survey • Study records
***Patient-level Maintenance*** Extent to which blood pressure improvements observed during the intervention phase are maintained	Active intervention (months 4–15) and maintenance (months 16–27) periods	• Medical charts • Study REDCAP form

*BP* blood pressure

*Adoption* will be determined as the percentage and representativeness of clinics that complete the blood pressure assessment protocol at the initial study step (i.e., did they roll out intervention? Yes/No). Intervention fidelity (*primary implementation outcome*) will be defined as the difference in percentage of patient visits with recorded blood pressure measurement between intervention and control periods. We will also keep track of adaptations made to the blood pressure assessment protocol via care coordinator notes and reports. Clinic-level *maintenance* of the intervention will be defined as the extent to which blood pressure continues to be assessed after the active intervention period ends based on medical chart reviews. We will also assess the normalization of the blood pressure assessment protocol using a 23-item questionnaire [32] healthcare workers will complete at the beginning and at the end of the maintenance period.

*Reach* will be defined as the percentage and representativeness of patients with elevated blood pressure that receive educational materials and lifestyle modification advice / medication, among all patients with elevated blood pressure. Changes in patient blood pressure (*primary effectiveness outcome*) will be defined as the difference in mean systolic blood pressure between the intervention and control periods. Patient-level m*aintenance* of intervention effects will be defined as the extent to which blood pressure improvements observed during the active intervention period are sustained during the maintenance period.

The *cost* evaluation will examine direct medical costs for intervention delivery, including implementation strategies, patient-facing intervention materials, additional staff time required to deliver the intervention, and additional blood pressure medication. One-time costs for implementation strategies will be estimated from the study records. The additional time burden associated with integrating the blood pressure assessment protocol in participating clinics will be assessed using a time and motion assessment in a random sub-sample of 100 patients at each clinic during control, active intervention, and maintenance periods (900 per period; total *n* = 2,700). This assessment will collect data on the start and end time of different procedures during a patient’s journey through a routine clinic visit. Finally, this patient subsample will also complete a survey regarding medical expenditures for outpatient and inpatient care utilization during the last 12 months, and the EQ-5D quality of life questionnaire [33] to determine health utility.

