The allocation sequence began with an observation period where none of the clinics had neither received the implementation strategies nor rolled out the patient intervention (Period 1). In this period, we collected implementation and clinical data under the control condition. After the control period, clinics crossed-over to the intervention condition, three at a time based on their randomization sequence. To date, all nine clinics have-crossed over to the active intervention period which will run from study months 4–15 (Periods 2–5). Since this intervention was randomized at the clinic level and involves providing clinical care, blinding was not possible. For each step, clinics were notified one month in advance prior to initiation of the intervention.

At month 14, all clinics will initiate a two-month offboarding transition period (Period 5). Here, research staff will support clinic staff to ensure that implementation strategies continue to be executed, while also helping them to further integrate the blood pressure assessment protocol within routine care. From months 16–27, research staff will be withdrawn from clinics and a maintenance observation period will begin (see Table 1).

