#### Costing, cost-effectiveness and budget impact analyses

These analyses will concentrate on direct medical costs including costs for intervention delivery and costs for outpatient and inpatient health care utilization, taking roughly a public healthcare system perspective. Time of healthcare staff for implementing the intervention will be valued according to average gross salaries including fringe benefits. The change in hypertension medication cost will be monetarized by multiplying the volume of hypertension medication with average market prices for hypertension medication. We will describe raw absolute accrued costs for each cost category in the intervention and control periods and stratified for the control, active intervention, and maintenance period. Since there is no value set for South Africa, we will use an established scoring algorithm developed for a neighboring country [41] to translate EQ-5D health states into health utilities. We will assess cost-effectiveness as the incremental cost per mmHg reduction in systolic blood pressure and the cost-utility as the incremental cost per quality adjusted life year gained [42]. Uncertainty in incremental costs, utility, and cost-effectiveness/cost-utility will be assessed through non-parametric bootstrapping methods [43]. We will report the cost-effectiveness plane and the cost-effectiveness acceptability curve for different willingness to pay thresholds for a gain in one quality adjusted life year. We will also conduct rough extrapolations to assess the expected intermediate- and long-term budget impact on population level [44, 45]. For these analyses, we will follow the Consolidated Health Economic Evaluation Reporting Standards 2022 [46].

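### The 12-month cost recall is as long as the longest possible active intervention period, so at least 600 of the 900 active-phase surveys mix control and intervention time and dilute the survey-based utilization difference

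*Protocol article*

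**What the plan says.** The cost paragraph under Outcome measures and definitions plans a time and motion assessment, whose sample is given as "random sub-sample of 100 patients at each clinic during control, active intervention, and maintenance periods (900 per period; total *n* = 2,700", and adds that "this patient subsample will also complete a survey regarding medical expenditures for outpatient and inpatient care utilization during the last 12 months". Table 3 lists the patient-reported cost survey as a source for cost-effectiveness.

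Under Study design, "clinics crossed-over to the intervention condition, three at a time based on their randomization sequence", with an "active intervention period which will run from study months 4–15 (Periods 2–5"). For maintenance: "From months 16–27, research staff will be withdrawn from clinics and a maintenance observation period will begin".

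Under Costing, cost-effectiveness and budget impact analyses, the article says "We will describe raw absolute accrued costs for each cost category in the intervention and control periods", and that these are "stratified for the control, active intervention, and maintenance period". Outpatient and inpatient utilization is one of the cost components there. The incremental cost feeds a cost per mmHg and a cost per quality-adjusted life year.

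The article does not give the survey month within a phase, does not say whether the questionnaire dates episodes, and states no rule for dividing the 12 months between conditions.

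**The concern.** Each answer covers a year, but it is filed under the phase in which the patient happened to be asked. A patient surveyed a few months after the clinic crossed over reports mostly visits and admissions from before the crossover, and these are counted as intervention-period costs. The control surveys do not have this problem, since everything they recall precedes crossover. The contrast is therefore contaminated on one side, which pulls the survey-based utilization difference towards zero.

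This matters because utilization costs enter both ratios and the budget impact, which the Discussion says are meant to inform decision-makers. For blood pressure, the article drops the first two months after initiation so that the effect has time to appear. It states no comparable safeguard for costs. If the survey yields only undated 12-month totals, a phase label cannot separate the conditions afterwards.

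**Working it through.** **Inputs from the article.** Recall window: 12 months. Active intervention: months 4–15. Maintenance: months 16–27. Three sequences of three clinics. Surveys: 100 per clinic per phase, which reproduces the stated totals: 100 × 9 = 900 per phase, and 900 × 3 = 2,700.

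**Assumed.** The crossover months are in Table 1, which is not reproduced in the text at hand. I take 4, 7 and 10, with 4/6/8 and 4/8/12 as a range. The survey month is not stated, so two cases are shown.

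**Step 1: what follows without assumptions.** The longest active period is 15 − 4 + 1 = 12 months, equal to the recall window. Only the first sequence, surveyed at the end of month 15, can have a window wholly under intervention. The other six clinics start after month 4, so none of their active-phase surveys can. That is 6 × 100 = 600 of 900 mixed surveys at the least.

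**Step 2: pre-crossover share of the window.** For a clinic that crosses over at the start of month c and is surveyed at the end of month m:

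share = max(0, 12 − (m − c + 1)) / 12

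| Survey timing | c = 4 | c = 7 | c = 10 | Mean |
|---|---|---|---|---|
| All at end of month 15 | 0% | 25% | 50% | 25% |
| Spread evenly over months c to 15 | 46% | 58% | 71% | 58% |

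Example for c = 7, spread evenly: the pre-crossover months run from 11 down to 3, with a mean of 7, and 7/12 = 58%.

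Over the other assumed crossover months, the month-15 mean runs from 17% (4/6/8) to 33% (4/8/12). For the even spread, counting surveys at mid-month instead of month end raises the mean to 62.5%, with a range of 58% to 67%.

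**Step 3: effect on the difference.** Let U be the true utilization cost difference for a full year under intervention and s the pre-crossover share. With a constant monthly effect and no time trend, the expected survey difference is (1 − s) × U. This is 75% of U for surveys at month 15 and about 42% of U for an even spread.

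**Step 4: effect on total incremental cost.** Strategy costs come from study records, staff time from the time and motion assessment, and medication from volume times price. Call their sum D. The true total is D + U and the estimated total is D + (1 − s)U, so the error is −sU. If the intervention raises utilization (U > 0), the total is understated. If it lowers utilization (U < 0), the saving is diluted and the total is overstated.

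**Step 5: maintenance surveys.** The share of the window before month 16 is (12 − (m − 15))/12, which averages 5.5/12 = 46% over m = 16 to 27 and reaches zero only at the end of month 27. Most of that is active-phase time, not control time. A window lies wholly after crossover when m ≥ c + 11, that is from months 15, 18 and 21 for c = 4, 7 and 10. Within months 16–27 the windows that still reach into control time number 0 + 2 + 5 = 7 of 36 sequence-months. The other 29 (81%) are wholly post-crossover.

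**The case against.** The strongest reply is that the size of the problem rests on facts the article does not give. The survey month is unstated and the crossover months are assumed. The questionnaire may already date episodes, and an economic analysis plan may already allocate them. This stands in part: the percentages are conditional, and if episodes are dated, only the allocation rule is lacking. It does not remove the point, because the recall length, the length of the active period and the reporting by phase are all stated, and step 1 needs nothing else.

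A second reply is that the design already offers a partial remedy. Clinic staff continue the strategies during maintenance, and most maintenance windows lie wholly after crossover. That stands, and it is used in the fix. Such a contrast does not isolate delivery by research staff, however.

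A third reply is that a long recall captures rare admissions, and that shortening it now would not match control surveys, since all nine clinics have already crossed over. That also stands, so a shorter window is not recommended. Nor is restriction to active-phase surveys with a clean window, because at most the month-15 surveys of three clinics would remain.

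Finally, this is one component of a secondary economic outcome, and neither co-primary outcome is affected.

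**Conclusion.** The point holds for the survey-based utilization costs. The recall window and the phases do not fit together, at least 600 of 900 active-phase surveys mix conditions, and reporting them by phase attenuates the outpatient and inpatient cost difference. With crossovers at 4/7/10, a constant monthly effect and no time trend, the loss is about 25% if all surveys are at month 15 and about 58% if they are evenly spread.

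Two stronger readings go further than the article allows. A reader might infer that the reported intervention costs are mostly control-period costs. That is so under an even spread but not for surveys at the end of the phase, and the article does not say which applies. A reader might also infer that the incremental cost as a whole is biased towards zero. Only one component is diluted, and the total can err either way. Even for that component, a time trend in costs could change the picture.

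**What to change.** In the remaining surveys, keep the 12-month recall but record the month of each outpatient and inpatient episode. Assign each episode to the clinic's condition in that month, with person-months in each condition as the denominator.

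For undated surveys already completed, replace the phase label in the cost model with the fraction of the recall window spent in each condition, computed from the survey date and the clinic's crossover month.

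As a check, report a control versus post-crossover contrast using surveys whose window lies wholly after crossover. These will come mostly from the maintenance phase, so state that the contrast does not isolate delivery by research staff.

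The cost is a slightly longer questionnaire, some error in dating episodes, and wider intervals than a simple comparison by phase would show. The exposure-fraction model also relies on the effect being constant from month to month.
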